## Abstract

**Introduction:**

The WHO’s Integrated Management of Childhood Illnesses (IMCI) algorithm for diagnosis of child pneumonia relies on counting respiratory rate and observing respiratory distress to diagnose childhood pneumonia. IMCI case defination for pneumonia performs with high sensitivity but low specificity, leading to overdiagnosis of child pneumonia and unnecessary antibiotic use. Including lung auscultation in IMCI could improve specificity of pneumonia diagnosis. Our objectives are: (1) assess lung sound recording quality by primary healthcare workers (HCWs) from under-5 children with the Feelix Smart Stethoscope and (2) determine the reliability and performance of recorded lung sound interpretations by an automated algorithm compared with reference paediatrician interpretations.

**Methods and analysis:**

In a cross-sectional design, community HCWs will record lung sounds of ~1000 under-5-year-old children with suspected pneumonia at first-level facilities in Zakiganj subdistrict, Sylhet, Bangladesh. Enrolled children will be evaluated for pneumonia, including oxygen saturation, and have their lung sounds recorded by the Feelix Smart stethoscope at four sequential chest locations: two back and two front positions. A novel sound-filtering algorithm will be applied to recordings to address ambient noise and optimise recording quality. Recorded sounds will be assessed against a predefined quality threshold. A trained paediatric listening panel will classify recordings into one of the following categories: normal, crackles, wheeze, crackles and wheeze or uninterpretable. All sound files will be classified into the same categories by the automated algorithm and compared with panel classifications. Sensitivity, specificity and predictive values, of the automated algorithm will be assessed considering the panel’s final interpretation as gold standard.

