**Figure 3 F3:**
[figure not shown]
Lung sounds recording positions.

A total of 11 paediatricians will be trained to the methodology developed and validated during the Pneumonia Etiology Research for Child Health (PERCH) study.^40^ Only paediatricians successfully standardised to the methodology will serve as human listening panel members. Panellists will classify the recorded sound files of all four positions separately into five categories, for example (1) no wheeze and no crackles, (2) wheeze only (no crackles), (3) crackles only (no wheeze), (4) both wheeze and crackles or (5) uninterpretable. Two primary listeners will independently classify the recorded lung sounds, and any discrepancies will be arbitrated by the third listener ([name]). The panellists and [name] will be blinded to the clinical information of the children. Johns Hopkins and Sonavi Labs developed a machine learning algorithm; all sound files will also be classified the same categories using this algorithm. This algorithm does not include the clinical information of the children and this will be blinded to the panel classification. Finally, both classification will be compared. Figure 4 depicts the study flow.

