### Sample size calculation

Cohen’s kappa will be used to assess interlistener and computer–human agreement in this study. To detect a true kappa of 0.50 compared with a kappa of 0.40 under null hypothesis and assuming two-sided type I error of 5%, power of 80% and two categories of frequencies equal to 30% and 70% normal and abnormal findings, respectively, a sample size of 752 will be required.^41^ This sample size has been calculated in Power Analysis and Sample Size software V.11.

We will include all quality recordings for this assessment. A quality recording is defined as a recording with >75% interpretable chest positions (ie, three of the four chest positions recorded are interpretable). Assuming that 75% of all recordings will be of acceptable quality, we will need 1003 subjects to be enrolled in this study to obtain our required sample size of 752.

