### Statistical analysis

A point estimate for the proportion of recordings along with a 95% CI that meets the definition of quality will be determined. The numerator will be the total number of recordings that were interpreted to meet quality criteria and the denominator will be the total number of recordings collected and interpreted. A raw agreement percentage will be determined between the interpretations of the two primary human listeners of the listening panel. The numerator will be the total number of recordings with an interpretation from the first and second human listener that agree, and the denominator will be the total number of recordings that have a final human interpretation from both primary listeners. Cohen’s kappa, a metric that assesses the agreement beyond chance will be calculated, and a kappa adjusted for prevalence and bias will also be calculated. A kappa above 0.8 will be defined as perfect agreement, 0.61–0.8 as high agreement, 0.41–0.6 as moderate agreement, 0.21–0.4 as fair agreement, 0.01–0.2 as low agreement and 0 as no agreement.

A raw agreement percentage between the overall human listening panel’s final interpretation result and the computerised analysis algorithm’s final interpretation result will be determined. The numerator will be the total number of recordings with an interpretation from the human listening panel and the computerised algorithm that agree, and the denominator will be the total number of recordings that have both a human and computerised interpretation. Cohen’s kappa, a metric that assesses the agreement beyond chance will be calculated, and a kappa adjusted for prevalence and bias will also be calculated. The same kappa scale detailed previously will be used for interpretation.

The performance of the computerised interpretation algorithm will be evaluated when assuming the human listening panel’s final interpretation is the gold standard. Sensitivity, specificity, positive predictive value, negative predictive value and positive and negative likelihood ratios will be assessed.

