## Discussion

This study aims to demonstrate the feasibility of collecting quality lung sounds by frontline health workers and to examine the performance of the machine learning algorithm against a panel of human listeners for identifying adventitial lung sounds. To our knowledge, this is the first study that will assess the recording of lung sounds of children younger than 5 years in first-level facilities by frontline workers in LMICs, where the burden of pneumonia and antibiotic use is high and diagnostic capacity is limited. The PERCH study enrolled children at a hospital setting and digital auscultation was performed by physicians, formally trained clinical assistants, or nurses,^40^ another study enrolled children at a tertiary level centre in Lima, Peru,^42^ and paediatricians recorded lung sounds in two tertiary level teaching hospitals in a study in Nepal.^43^ Recording lung sounds in a first-level facility poses unique challenges in that clinics are typically crowded and the environment can be chaotic and noisy. Furthermore, ill children younger than 5 years of age can be especially uncooperative in uncomfortable ambulatory settings, leading to unique challenges like agitation, crying, vocalisations and the associated auscultation artefacts these create. Healthcare providers in ambulatory settings may lack the necessary time to calm the child and address these issues due to pressures from a high patient volume. If frontline health workers can effectively use digital auscultation in their typical clinical setting, then many false-positive pneumonia cases may be spared from treatment with antibiotics, which may reduce the cost of treatment as well as reduce the chance of developing antimicrobial resistance. A systematic analysis of 132 national surveys from 73 countries reported that on average, 4 of 10 ill children below age 5 years in LMICs are treated with antibiotics.^44^ Recently, United Nations General Assembly announced that antimicrobial resistance is the most important and urgent threat globally.^45^

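### The unit of analysis for agreement and accuracy shifts between the sound file and the child, and no rule combines four position labels into one result per child

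*Protocol article*

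**What the plan says.** The protocol article uses two units.

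**The file.** Under Study design and procedure, "Panellists will classify the recorded sound files of all four positions separately into five categories". The algorithm then labels the same files, and the two sets of labels are compared. The abstract says the same: "All sound files will be classified into the same categories by the automated algorithm and compared with panel classifications".

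**The child.** Objectives and hypotheses defines quality per patient, as three of four positions interpretable. Sample size calculation uses the same three-of-four definition for a quality recording, so a recording there is one child's set of four. It gives the target as "a sample size of 752 will be required" and inflates it to 1003 enrolled subjects.

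**Unclear.** Statistical analysis counts recordings on which panel and algorithm agree, and refers to a final interpretation from each. It then says "Sensitivity, specificity, positive predictive value, negative predictive value and positive and negative likelihood ratios will be assessed", with no unit attached. No section says how four position labels become one label per child, for either the panel or the algorithm.

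**The concern.** The only comparison described in concrete terms is file against file, while the study was sized on children. These are different estimands with different numbers of units. One of them has clustered observations, for which intervals that assume independence would be too narrow.

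The choice affects the headline results. The second hypothesis is a kappa above 0.8 between algorithm and panel, and kappa depends on the unit. Specificity also matters: the Introduction gives the low specificity of the current case definition as the reason for the work, and the Discussion suggests that "many false-positive pneumonia cases may be spared from treatment with antibiotics". A case is a child, so readers will tend to take the reported specificity as the chance that a child without adventitious sounds is called normal. A file-level figure does not give that. With the text open to both readings, the unit could also be settled after the labels have been compared.

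**Working it through.** **1. The plan's own figure.** Inputs from Sample size calculation: "To detect a true kappa of 0.50 compared with a kappa of 0.40 under null hypothesis"; two-sided 5% error; 80% power; "two categories of frequencies equal to 30% and 70% normal and abnormal findings, respectively". For two raters with equal margins,

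n = [(z₀.₉₇₅·√τ²(κ₀) + z₀.₈₀·√τ²(κ₁)) / (κ₁ − κ₀)]²,

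where τ² is n times the large-sample variance of Cohen's kappa. With margins 0.3 and 0.7, √τ²(0.40) = 0.993 and √τ²(0.50) = 0.945, so

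n = [(1.960 × 0.993 + 0.842 × 0.945) / 0.10]² = 751.7, that is 752.

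Inflation: 752 / 0.75 = 1002.7, that is 1003. Both figures reproduce, and the units are children.

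**2. Units in a file-level analysis.** The 752 qualifying children supply between 752 × 3 = 2256 and 752 × 4 = 3008 interpretable files. With within-child correlation ρ and m files per child, the design effect is 1 + (m − 1)ρ. For m = 4 and an assumed ρ of 0.3 it is 1.9, so 3008 files carry the information of about 3008 / 1.9 = 1583. At ρ = 0.8 it is 3.4, and the figure is about 885.

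**3. From file specificity to child specificity.** The documents give no file-level accuracy, no within-child correlation and no combining rule, so all of these are assumptions. Take a child with four truly normal positions, under the rule that any abnormal position makes the child abnormal.

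- Independent errors: child specificity = Sp⁴, for example 0.90⁴ = 0.656. With three interpretable positions, 0.90³ = 0.729.
- Correlated errors (beta-binomial): product over i = 0 to 3 of (b + i)/(a + b + i), with a = (1 − Sp)(1 − ρ)/ρ and b = Sp(1 − ρ)/ρ. For Sp = 0.90 and ρ = 0.3: 0.900 × 0.930 × 0.946 × 0.956 = 0.757.

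| Assumed file specificity | ρ = 0 | ρ = 0.3 | ρ = 0.8 |
|---|---|---|---|
| 80% | 41% | 56% | 74% |
| 90% | 66% | 76% | 87% |
| 95% | 81% | 87% | 93% |

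**4. The same step under another rule.** If two or more abnormal positions are needed, independent errors at 90% give 0.90⁴ + 4 × 0.10 × 0.90³ = 0.656 + 0.292 = 0.948. That is above the file value.

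**5. All measures together.** Simulation of 400,000 children. Each position of an abnormal child is abnormal with probability 0.5, with at least one forced. File sensitivity is 85% and file specificity 90%. The any-position rule is applied to both panel and algorithm.

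| Abnormal children | ρ | Child specificity | PPV, file → child | Kappa, file → child |
|---|---|---|---|---|
| 30% | 0 | 66% | 61% → 55% | 0.65 → 0.51 |
| 30% | 0.3 | 76% | 61% → 62% | 0.65 → 0.61 |
| 70% | 0 | 66% | 83% → 87% | 0.75 → 0.66 |
| 70% | 0.3 | 76% | 83% → 90% | 0.75 → 0.71 |

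Child sensitivity was 93% to 96% against 85% per file. At 70% abnormal with independent errors, NPV fell from 91% to 87%. When 30% of children were abnormal, only 16% of files were, so predictive values per file and per child rest on different prevalences. With the two-of-four rule applied to both sides, child specificity in the four scenarios, in table order, was 93%, 89%, 87% and 86% against 90% per file.

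**The case against.** **The unit may already be the child.** Statistical analysis never mentions files. It counts recordings, and Sample size calculation uses that word for a child's set. Labelling positions separately is a necessary input to any child-level result. This stands in part: a reader might infer that the plan has fixed the file as the unit for sensitivity and specificity, and it has not. But a child-level reading needs a combining rule, and none is given.

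**File-level specificity need not overstate.** A reader might infer that it always does. The documents do not support this, because they contain no any-position rule. A two-of-four rule can move specificity either way, and positions in one child share a session and a noise environment, so independence is the extreme case. This objection stands, and the figures above are conditional.

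**PPV is not generally flattered.** It was higher per child in three of the four scenarios, including both at 70% abnormal, the share used in Sample size calculation. This stands too.

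**The objective concerns lung sounds.** Performance on lung sounds is the stated second objective, and sound-level accuracy is a legitimate target for it. Antibiotic sparing is motivation and a conditional remark, not an endpoint, and the Discussion leaves decision-making to later trials. This is a reason to keep the file-level results. It does not resolve the mismatch with the unit that was sized.

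**A combining rule is ordinary SAP content.** If it were merely absent, that would answer the point. Here the published sections pull in different directions on the unit, and a reader cannot reconcile them.

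**Conclusion.** The point holds as an inconsistent and undefined unit of analysis. Comparison is described per file, quality and sample size are per child, and nothing connects the two. File-level kappa and accuracy therefore cannot be read as child-level values. Under an any-position rule and an assumed file specificity of 90%, child specificity lies between about 66% (independent errors) and 87% (ρ = 0.8). Sensitivity is higher and kappa was lower in all four scenarios. Predictive values go either way, and under other rules so does specificity. These sizes rest on assumed accuracy, correlation, prevalence and rule, so they show how much the choice can matter and do not predict the result. The point does not extend to the sample size, which is correct on its own inputs.

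**What to change.** In Statistical analysis:

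1. Name the unit for kappa and for each accuracy measure.
2. Prespecify one combining rule, applied identically to panel and algorithm. One example is abnormal if an adventitious sound is found at any interpretable position, among children meeting the three-of-four criterion.
3. Report kappa, sensitivity, specificity, predictive values and likelihood ratios per child, matching the 752 that were sized, alongside the file-level results.
4. Give the file-level estimates intervals that allow for clustering within child, for example from a bootstrap that resamples children.

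This uses data already being collected and leaves 752 and 1003 unchanged. The cost is a few sentences, one extra table, and a reported specificity that may be lower than the file-level figure.

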**Ethics and dissemination:**

The study protocol was approved by the National Research Ethics Committee of Bangladesh Medical Research Council, Bangladesh (registration number: 09630012018) and Academic and Clinical Central Office for Research and Development Medical Research Ethics Committee, Edinburgh, UK (REC Reference: 18-HV-051). Dissemination will be through conference presentations, peer-reviewed journals and stakeholder engagement meetings in Bangladesh.

**Trial registration number:**

NCT03959956.

Strengths and limitations of this studyEvaluating the quality of lung sound recordings in a first-level facility where auscultation is usually unavailable and challenging to obtain due to a typically crowded and noisy environment and providers may not get enough time to calm the child due to time pressure from a high-volume patient.This study will assess the feasibility of recording lung sounds by frontline community health workers who do not usually use conventional stethoscopes during clinical care.Two standardised paediatricians masked to the child’s clinical status will independently classify the recorded lung sounds, and a third masked and independent paediatrician will arbitrate any discrepancies.A machine learning algorithm developed by Johns Hopkins and Sonavi Labs will detect abnormal lung sounds and be compared with classifications by human listeners/paediatricians.The study will not have chest radiography findings of enrolled children, which is considered by many a gold standard for pneumonia diagnosis, as chest radiography is not available at this level of the health system in Bangladesh.

## Introduction

Childhood pneumonia is one of the leading causes of death in children younger than 5 years globally^1^ and accounts for an estimated 0.8 million deaths in children annually.^2^ The WHO estimates that the African and the South-East Asian Regions contribute to more than 75% of total paediatric deaths from pneumonia.^3^ It is estimated that the annual incidence of childhood pneumonia in low- and middle-income countries (LMICs) is 231 episodes per 1000 children.^3^ Pneumonia is also a significant cause of hospitalisation,^4^ and about 16.4 million children in LMICs were hospitalised due to pneumonia in 2015.^3^ A population-based study in Bangladesh estimated that the annual incidence of pneumonia was 360 episodes per 1000 child-years, of which 7.3% were hospitalised.^5^ The case-fatality rate of child pneumonia in Bangladesh is estimated to be 2%–4%.^6 7^

The WHO and UNICEF Integrated Management of Childhood Illness (IMCI) guidelines have been the foundation of pneumonia management in LMICs since mid-90s.^8 9^ Per current IMCI guidelines, a child with fast breathing and/or chest indrawing without any danger sign is classified as non-severe pneumonia and treated at home with oral antibiotics.^10^ These guidelines have proven to be one of the most important childhood pneumonia interventions for LMICs to date, and up to 36% of the under-5-year-old mortality reductions in LMICs have been attributed to guideline implementation.^11–15^

Despite its overall success, the IMCI algorithm for diagnosis of child pneumonia can still be improved. First, the guidelines were developed when access to vaccines was limited and child pneumonia mortality was high, so the guidelines intentionally prioritised sensitivity over specificity to ensure children with possible bacterial disease received antibiotics.^8 10^ Thus, the IMCI algorithm overdiagnoses many children with pneumonia who do not require antibiotics and they may have different treatable diseases.^16 17^ Second, the WHO guidelines do not include lung auscultation in their pneumonia definition for frontline healthcare workers despite lung auscultation serving as the cornerstone for pneumonia diagnosis in most ambulatory, well-resourced settings staffed by clinicians trained to perform lung auscultation.^10^ The exclusion of auscultation findings in these guidelines likely stems from its high interobserver variability and subjectivity, regardless of the training level of healthcare providers, and the related difficulty in training healthcare workers to effectively use a conventional stethoscope.^18–22^ Traditional stethoscopes themselves are also limiting, attenuating higher frequency sounds, like wheezing and crackles, yet transmitting ambient noises and tubular resonance effects.^20 23 24^ Automated real-time classification of lung sounds or digital auscultation may overcome these limitations.^25^ Digital auscultation augmented by artificial intelligence algorithms has the potential to be a highly specific respiratory diagnostic tool feasible for use by front line healthcare workers in LMICs. Operationally, the inclusion of adventitious sound classifications in current IMCI guidelines could help to reduce^26^ unnecessary use of antibiotics in LMICs.

A digital stethoscope can convert an acoustic sound to electronic signals, which can be further amplified for optimal listening. These electronic signals can then be processed and digitalised to transmit to a personal computer or a laptop.^27^ Automatic lung sound analysis, aiming to overcome the limitations of conventional auscultation, has been the recent focus of a significant amount of research, and some commercial systems are already available in the market.^28 29^

The digital stethoscope has advantages over the analogue stethoscope in different stages of auscultation. An analogue stethoscope requires the proper placing of the diaphragm or bell in the correct positions of the human body to listen to internal body sounds. More modern digital stethoscopes do not necessarily require exact placement for two reasons. First, they convert the acoustic wave into electric signals and replace the double-sided chest piece (diaphragm and bell) with transducers to convert acoustic signals to electric signals. Second, the chest piece is packed with transducer arrays to achieve a uniform sensitivity over the entire active area. Together, this design delivers a strong signal even when the chest piece is not placed in precisely the right position.^30 31^ This advantage is essential for minimally trained healthcare providers.

Conventional auscultation using an analogue stethoscope also requires a quiet environment, and ideally with the patient in a quiet, cooperative state, which is difficult in hospitals/clinics and especially hospitals/clinics in LMICs where the number of patients are typically usually higher than capacity. This often results in patient examination rooms filled with chattering people, ringing phones and whirring fans; most importantly, the child being examined may then be agitated, uncooperative and/or crying. Digital stethoscopes could improve listening capability through the use of noise cancelling technologies.^32 33^ Limitations of the human auditory system, which ranges from 20 Hz to 20 kHz for young adults and the range shrinks after middle age,^34^ are also a drawback in conventional auscultation using a conventional stethoscope. A digital stethoscope can amplify sounds up to 100-fold.^35^ Much experience is required to interpret body sounds, and inter-rater variability is high regardless of healthcare providers’ training level.^21^ Machine learning techniques can be used in digital auscultation to auto-analyse sounds^28^ and produce a diagnosis or treatment decision.^23^

Johns Hopkins University and Sonavi Labs developed a novel digital stethoscope named Feelix Smart Stethoscope (figure 1),^30 31^ which improves lung signal strength by uniformly distributing highly sensitive microphones in an array pattern across the stethoscope diaphragm to increase the sensitivity and provide broader frequency response, a critical feature for identifying higher frequency pathologic lung sounds. Its 3.7 V and 250 amps/hour rechargeable battery can power >20 hours of use, important in rural communities with unreliable electricity. The device mitigates movement artefact and tubular resonance by using an ergonomic design to better secure the device on the child’s chest. It also eliminates the rubber stethoscope tubing, a source of ambient noise and friction contamination. Notably, the device includes an integrated external facing microphone that captures simultaneous environmental noise to the lung sound recording and removes the unwanted ambient noises through an adaptive spectral subtraction schema.^24 36^ The Feelix Smart Stethoscope also permits onboard data storage with a micro SD card. The device turns on when the user picks up the device or touches the top of the device. The device turns off automatically after 60 s when it does not sense any touch. The device has three touch buttons—button 1 to start recording, button 2 to start a new session to record a new child’s four chest points recording, and button 3 to establish a Bluetooth connection with a mobile phone or tablet. It also has a slider to control sound volume level. In each session, the device automatically records 10 s for each four chest points of a child. The Feelix Smart Stethoscope has been successfully validated in the laboratory against six other commercially available electronic stethoscopes—including the Littmann 3200 electronic stethoscope and Thinklabs—and has demonstrated comparable results.^37 38^ Johns Hopkins and Sonavi Labs developed a machine learning algorithm that can provide an automated classification of adventitious lung sounds. This Feelix Smart Stethoscope and the machine learning algorithm will be used in this study.

